### Interim analyses

Interim analyses are not planned.

### Methods in analysis to handle protocol non-adherence and any statistical methods to handle missing data

No statistical methods will be used to compensate for missing data.

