**Fig. 1 Fig1:**
[figure not shown]
The order of stimulation patterns. The order of stimulation patterns of DTM or tonic is randomly assigned to two courses. One course is DTM stimulation (Stim-1), then tonic stimulation (Stim-2). The other course is in reverse order. Each stimulation pattern is performed for two days. The stimulation off period is set as one day between Stim-1 and Stim-2 (Stim-off)

After the SCS trial, the inserted leads are removed whether or not analgesic effects are obtained. In cases of an effective SCS trial or the patient agrees to implantation of an SCS system even after a non-effective SCS trial, the second step follows. With an interval of 1 month from the SCS trial, a paddle-type lead is placed on the rostral side of the SCI by laminectomy under general anesthesia (Fig. 2). The location of the lead is confirmed by intraoperative X-ray and motor-evoked potential monitoring. At the same time, an implantable pulse generator (IPG) (Intellis; Medtronic Inc.) is implanted on the hip, and it is connected to the paddle-type lead. After the SCS implantation, an effective stimulation pattern that showed efficacy in the SCS trial is started, and the analgesic effects are evaluated. In the absence of analgesic effects in the previous SCS trial, DTM stimulation is tried.

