### Criteria for discontinuing or modifying allocated interventions

Any patients requesting to end their participation in the study can be withdrawn from the study regardless of the stage they have reached in the study process. Patients do not have to provide the reason of withdrawal. Patients found to be pregnant or those judged ineligible to continue participating in the study by the investigators will also be withdrawn from the study.

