### Clinical assessments

At entry, clinical research physicians obtain information from patients regarding age, sex, past history, medications, cause of SCI (traumatic or non-traumatic), level of SCI (cervical, thoracic, lumbar), location of pain (arm, leg, lower back, back, chest), degree of paralysis (none, mild, moderate, severe), sensory disturbance (hypoesthesia, allodynia, numbness), duration of disease, and Frankel grade (B-E). During the SCS trial, the degree of pain is evaluated using a VAS according to the plan (Table 1). After SCS system implantation, assessment items are evaluated according to the plan, including degree of improvement of pain relief, mental health, comprehensive health, and gait function (Table 1). Six months after SCS system implantation, if no improvement of any of the assessment items is seen, removal of the implanted SCS system would be considered.

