### Primary outcome

Pain improvement is defined as more than a 33% reduction in the VAS score. The primary outcome is rates of achieving pain improvement at 3 months after SCS system implantation.

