### Statistical analysis

The primary outcome will be estimated as the probability of patients achieving more than 33% pain improvement on the VAS at 3 months after SCS system implantation. The secondary outcome analyses are as follows:A logistic regression analysis using stimulation timing (Stim-1, Stim-2), stimulation pattern (tonic, DTM), pre-VAS values for each stimulation, and interaction between stimulation timing and stimulation pattern as explanatory variables. The carryover effect is examined by testing the interaction term at a significance level of 10%. If a carryover effect is observed, an additional analysis will be performed using only Stim-1.Adjusted means and 95% confidence intervals (CIs) of the rate of change or amount of change for each item (VAS, SF-MPQ-2, PCS, QIDS-J, and SF-36^®^) are calculated for each evaluation time point including pre-implantation and post 1, 3, 6, 12, 18, and 24 months using linear mixed models with time points as fixed effects. The amount of change of each item at each time point is compared after using the Dunnet-Hsu correction for multiple comparisons.For the patients undergoing implantation, logistic regression will be performed to investigate the relationship between the efficacy of the SCS trial (DTM) and the effectiveness for 33% improvement on the VAS at 3 months after implantation.Preoperative factors associated with long-term effects are examined using logistic regression analysis as explanatory variables for the following items: sex, age (<60 years vs. ≥60 years), disease duration, pain site (arm, leg, lower back, back, chest), level of SCI (cervical, thoracic, lumbar), paralysis (none, mild, moderate, severe), sensory disturbance (hypoesthesia, allodynia, numbness), and Frankel classification (B, C, D, E).Probability of gait improvement is estimated, defining an improvement as 1 point or more in the FAC category. The probability of improved cases and the 95% CIs will be calculated at each evaluation time point.

Safety analysis will be performed by tabulating the number and probability of each event.

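### Followed as written, the missing-data rule makes the 3-month response rate an observed-case rate, with no count for patients lost before that visit

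*Protocol article*

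**What the plan says.** All references are to the protocol article.

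- **Primary outcome**: "The primary outcome is rates of achieving pain improvement at 3 months after SCS system implantation". **Statistical analysis** adds: "The primary outcome will be estimated as the probability of patients achieving more than 33% pain improvement on the VAS at 3 months". Neither section says which patients form the denominator.
- The section **Methods in analysis to handle protocol non-adherence and any statistical methods to handle missing data** consists of a single sentence: "No statistical methods will be used to compensate for missing data".
- **Study procedures** (text after Fig. 1) sets the entry to the second step: "In cases of an effective SCS trial or the patient agrees to implantation of an SCS system even after a non-effective SCS trial". Other patients do not go on to implantation.
- **Criteria for discontinuing or modifying allocated interventions**: patients who ask to stop "can be withdrawn from the study regardless of the stage they have reached in the study process", and "those judged ineligible to continue participating in the study by the investigators will also be withdrawn from the study". No outcome value is assigned to either group.
- **Clinical assessments**, at 6 months after implantation: "if no improvement of any of the assessment items is seen, removal of the implanted SCS system would be considered".
- **Sample size**: 10, from an expected 2 to 4 eligible cases a year over 3 to 5 years. The text does not say whether 10 means enrolled or implanted.

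**The concern.** Patients are randomised before the SCS trial, but the primary outcome exists only for those who are implanted and then measured 3 months later. Between these points patients can leave in two ways: by not going on to implantation, or by withdrawal after it. The article's one rule on missing values gives neither group an outcome.

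At least part of this loss may be related to response. Not being implanted can follow a non-effective SCS trial. The Discussion itself expects that caudal leads may give too little relief, and that the trial period gives patients time to decide. With 10 patients and no control arm for this outcome, each patient left out shifts the headline rate by several percentage points, and nothing offsets the shift.

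A similar question arises later. A patient considered for removal at 6 months because no assessment item improved is, by that criterion, a gait non-improver at that visit. If no later FAC value is collected, the same rule drops that patient from the 12- to 24-month gait proportions.

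**Working it through.** **1. The plan's own figure.** Expected cases per year times years: 2 × 5 = 10 and 4 × 3 = 12. The stated size of 10 is consistent with this feasibility argument. It rests on no response rate, precision target or loss allowance.

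**2. Who has a 3-month value.**

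| Path | 3-month VAS | Under the stated rule |
|---|---|---|
| Implanted, assessed at 3 months | yes | counted |
| Implanted, withdrawn before 3 months | no | in neither numerator nor denominator |
| Not implanted after a non-effective SCS trial | none possible | not visible in the result |
| System removed at 6 months or later for lack of improvement | already obtained | counted; the 3-month rate is unaffected |

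**3. Formula.** Let N be the patients who started, m those without a 3-month VAS, and k the responders.

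- Observed-case rate: k / (N − m)
- Rate with missing counted as non-response: k / N
- Gap: k·m / [N(N − m)], which is zero if m = 0 and positive whenever k and m are both above zero

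**4. Numbers.** N = 10 is the plan's size, taken here as enrolled. The values of k and m are assumptions, because the article gives neither a response rate nor a loss rate. Intervals are exact (Clopper-Pearson) 95%. For k = 5:

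| m | Observed-case rate | 95% CI | Gap to 5/10 = 50.0% (18.7–81.3%) |
|---|---|---|---|
| 0 | 5/10 = 50.0% | 18.7–81.3% | 0 |
| 1 | 5/9 = 55.6% | 21.2–86.3% | 5.6 points |
| 2 | 5/8 = 62.5% | 24.5–91.5% | 12.5 points |
| 3 | 5/7 = 71.4% | 29.0–96.3% | 21.4 points |
| 4 | 5/6 = 83.3% | 35.9–99.6% | 33.3 points |

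Check for m = 2: 5 × 2 / (10 × 8) = 0.125. Over k = 3 to 6 and m = 1 to 4, the gap runs from 3.3 points (3/9 against 3/10) to 40 points (6/6 against 6/10). If 10 means implanted patients, the same arithmetic holds with m counting only implanted patients lost before 3 months; those never implanted come on top.

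**5. Separating the two kinds of loss.** Suppose that of 10 who started, one is not implanted, one is implanted and withdrawn before 3 months, and 5 respond.

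- Observed cases: 5/8 = 62.5%
- All implanted, missing as non-response: 5/9 = 55.6%
- All who started: 5/10 = 50.0%

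The three rates answer different questions, and the article does not say which one it will report.

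**6. Later visits.** FAC is one of the listed assessment items, and Statistical analysis plans the proportion with FAC improvement at each evaluation time point. With f improved among n implanted and r removed without later FAC values, the reported proportion is f / (n − r) instead of f / n. The r patients are already known not to have improved at 6 months. Whether they are still measured after removal is not stated.

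**The case against.** The strongest reply is that analysis sets are usually defined in the full protocol or the analysis plan, which are not shown. An unnamed denominator in an article is then no defect by itself. That is right, and it is why the point rests on the missing-data sentence. That sentence is a stated rule, and a later plan that scored missing values as non-response would sit badly with it.

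Four stronger readings are tempting and should not be drawn:

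- *That the article starts the primary denominator at implantation.* This is a natural reading of the endpoint, but it is not stated. The only explicit restriction to implanted patients belongs to the analysis relating the SCS trial result to the 3-month effect.
- *That removal for lack of improvement inflates the primary rate.* It is considered at 6 months, after the primary time point.
- *That a long-term responder rate would be overstated.* No such rate is planned. The effect lasting more than 12 months is analysed by logistic regression on preoperative factors, and FAC is the only efficacy proportion planned beyond 3 months. Nor does the article say that patients leave follow-up after removal.
- *That everyone not implanted must count as a failure in the primary result.* The hypothesis concerns a paddle lead rostral to the injury, and these patients never received one. The effect among implanted patients is a legitimate target.

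It is also fair that the link between loss and poor response is plausible but not shown. Patient request, pregnancy and ineligibility are the listed withdrawal grounds, and patients may be implanted after a non-effective trial. The study is exploratory, with no test or threshold on the primary outcome, and the intervals above overlap widely. This limits the weight of the point, but an implanted patient without a 3-month VAS still has no classification.

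**Conclusion.** The concern holds in a limited form. As written, the plan yields an observed-case proportion in which implanted patients lost before 3 months disappear and patients never implanted are not visible. Relative to counting them as non-responders, the error has one direction, upward. Its size depends wholly on the number lost: zero with no losses and 12.5 points in the illustration of 5 responders with 2 of 10 unassessed. Those counts are assumptions.

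The 3-month rate is not affected by removal at 6 months. The later consequence is conditional: if removed patients have no further FAC values, known non-improvers leave the 12- to 24-month gait proportions, and they could leave the analysis of effect beyond 12 months.

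**What to change.** 1. Name all implanted patients as the denominator of the primary rate. Count an implanted patient without a 3-month VAS as a non-responder. Give an exact (Clopper-Pearson) 95% CI.
2. Report alongside it, as a named supportive estimate, responders divided by all enrolled patients who started the SCS trial, and state the number not implanted.
3. In the FAC proportions and the analysis of effect beyond 12 months, count patients whose system was removed for lack of improvement as not improved from removal onward.
4. Reword the missing-data section so that it agrees with items 1 to 3.

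The cost is a few sentences of analysis text, with no change to procedures or visits. If patients are lost, the reported rates become slightly less favourable. The change should be made before outcome data are seen; the article puts completion of recruitment at March 2028.

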### Plans to give access to the full protocol, participant-level data, and statistical code

Details of the full protocol, participant-level data, or statistical code will not be publicly available. Unpublished data will be made available upon reasonable request to the corresponding author of the publication.

### Oversight and monitoring

#### Composition of the coordinating center and trial screening committee

Nagoya University will serve as the coordinating center. Only the investigators and members of the data center will have access to the anonymized data in REDCap.

#### Composition of the data monitoring committee, its role and reporting structure

Two participating researchers at Nagoya University Hospital will monitor the data. They have the responsibility of verifying patients’ eligibility, written informed consent, compliance with the protocol, and accuracy of the data in REDCap.

#### Adverse event reporting and harms

Researchers will immediately report serious adverse events associated with the trial to the chief investigator. Then, the chief investigator will report serious adverse events to the director of the hospital and the principal investigator. Data about all serious adverse events will also be collected in REDCap.

#### Plans for communicating important protocol amendments to relevant parties

Any protocol modifications will be reviewed by the Certified Review Board of Nagoya University Graduate School of Medicine and then registered at jRCT. All relevant information will be shared among the researchers.

#### Dissemination plans

The results of this study will be published in a peer-reviewed journal and presented at national and international medical congresses.

## Discussion

In general SCS procedures, the SCS lead is placed at the same position in the SCS trial and in SCS system implantation. The appropriate SCS lead position for achieving pain relief is the rostral side of the SCI. However, in patients with past spinal surgical histories, adhesions around past spinal surgeries make it difficult to pass the cylinder-type leads through the SCI site. On the other hand, paddle-type lead placement is more invasive than insertion of cylinder-type leads because it requires laminectomy under general anesthesia. Therefore, an SCS trial using a paddle-type lead is not reasonable. In this study protocol, the SCS trial is planned using cylinder-type leads placed on the caudal side of the SCI. The SCS lead positions are not theoretically appropriate on that side and may not show sufficient pain relief effects. The reasons for performing this SCS trial are as follows. The first reason is to avoid the risk of bleeding or tissue damage by passing the cylinder-type leads through the SCI site. The second reason is to assess whether the result of the SCS trial with caudal stimulation of the SCI is a predictor of the long-term effects of SCS implantation with rostral stimulation of the SCI. The last reason is to provide patients time to decide on permanent SCS system implantation.

The cutoff line for determining whether a treatment is a success or not is important. The 30% to 40% range in pain reduction is widely used as a standard for clinically significant improvement. Hanley et al analyzed the relationship of pain intensity and meaningful change in pain for chronic pain after SCI and amputations [37]. They concluded that a 33% decrease in pain was a reasonable standard for meaningful change for chronic pain after SCI, and 30% may be low. Based on the report, the cutoff line for the primary outcome is set as more than 33% improvement in pain relief in this study. In assessing the effects of multiple stimulation patterns during an SCS trial, there are two main biases. One is the order of stimulation, and the other is the residual effect of previous stimulation. To reduce the former bias, the SCS trial is randomly assigned as DTM and tonic stimulation, followed by their crossover. To reduce the latter bias, a 1-day off period after a previous stimulation is set to wash out the residual effect.

## Trial status

This manuscript is based on the protocol (version 2, last updated on October 5, 2022). The first patient will be recruited in 2023. Recruitment will be completed by March 2028

## Data Availability

Any data required to support the protocol can be supplied on request.

## Abbreviations

CIs: Confidence intervals
CT: Computed tomography
DTM: Differential target multiplexed
EDC: Electronic data capture
FAC: Functional ambulation categories
IPG: Implantable pulse generator
jRCT: Japan Registry of Clinical Trials
MRI: Magnetic resonance image
PCS: Pain catastrophizing scale
QIDS-J: Quick inventory of depressive symptomatology
REDCap: Research electronic data capture
SCI: Spinal cord injury
SCS: Spinal cord stimulation
SF-MPQ-2: Short-form McGill pain questionnaire-2
SF-36^®^: Short-Form 36-item Health Survey
VAS: Visual analog scale
